#### Secondary analysis

The between-group differences for the secondary outcome considering the change in neuropathic symptoms, sciatic neurodynamic, conditioned pain modulation, and psychosocial factors from baseline to each 5, 10- and 26-weeks after randomisation will be calculated using mixed linear models using the interaction terms of treatment group versus time.

#### Tertiary analysis

The patients’ adherence, serious adverse events or adverse events, and patient satisfaction will be described and presented as mean and standard deviation for continuous variables and as absolute values and percentage for categorical variables.

We will also carry out the mediation analysis to understand whether sociodemographic factor, pain characteristics, and psychosocial factors affect the primary outcomes. The mediator’s analysis will be performed by simple mediation analysis, considering one variable per model, and we will use data collected at baseline. Models will be designed separately for pain intensity and functional limitation, considering the treatment group as independent variable (X), pain intensity and functional limitation as dependent variable (Y), and sociodemographic factor, pain characteristics, and psychosocial factors as mediators (M).

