### Randomisation, allocation, and blinding procedures

After the initial assessment, participants will be randomised to one of two groups; neural management plus advice versus advice alone (1:1 allocation). The allocation sequence will be prepared a priori using the "Research Randomizer", an online random number generator available at https://www.randomizer.org/. The randomisation of the participants will be performed using randomly permuted blocks of 4 and 6.

An independent examiner not involved in the study recruitment, assessment, or data analysis will allocate participants to the randomised group to ensure secret allocation from participants. Concealed allocation will be granted using numbered, sequentially ordered, sealed opaque envelopes with an index card written in which intervention group the participant will be enrolled. The envelopes will be numbered consecutively. The same examiner will open the sealed envelopes after the informed consent form has been completed, and the participant carries out the initial assessment. The participants will receive a unique study enrolment number and be referred to the physiotherapist responsible for the intervention group in which the participant was allocated.

Subsequently, the interventions will be performed by the physiotherapist’s authors ([name] and [name]) at the outpatient physiotherapy. The physiotherapists will be blinded to the initial assessment. The physiotherapist ([name]) responsible for assessing pre-treatment, during, and post-treatment will be unaware of randomisation and be blinded to treatment allocation. Statistical analysis will also be conducted blinded to group allocation. Due to the nature of the interventions, physiotherapists and participants will not be blind to treatment allocation. To guarantee that the treatment expectation is evenly balanced between the groups, the participants will not know the study hypothesis. The unblinding of the study will occur in case any serious adverse event occurs or once the completion of the research and the data analysed and interpreted.

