### Data collection and management

Patient’s characteristics at baseline assessment will be collected immediately before randomisation. All the data collected, and outcomes will be obtained using printed questionnaires. The original data will be scanned as image files by a research assistant and shared with a second research assistant. Data integrity will be audited by regularly scrutinising data for omissions and errors by double entered with automated checks in Microsoft Excel spreadsheet (Microsoft Corporation) performed by [name] remotely. Discrepancies will be explored and resolved by checking the original data.

Participants will be identified by an individual trial number to ensure confidentiality, and confidentiality regarding the data collected in all stages will be guaranteed by stored on password-protected servers. The paper-form data will be stored in locked filing cabinets at the Postgraduate Program in Rehabilitation Sciences. Data will only be accessible to the research team. All statistical analyses will be performed using the individual number of each participant and the statistician will be blinded to the group. The results will be presented by group data and any individual data will be spread to ensure confidentiality is preserved.

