#### Baseline assessment

Participants will be referred for baseline assessment consisting of the demographic (age, sex, weight, height, house income, marital state, profession, and education level), clinical (comorbidities, duration of pain, location of pain on the body map, average pain intensity, pain area, and medication), and lifestyle (physical activity and quality of sleep).

Physical activity will be evaluated using the short International Physical Activity Questionnaire (IPAQ) and categorised as low (<600 MET x min/week or <150 minutes per week of moderate intensity physical activity), moderate (600–3000 MET x min/week or 150–750 minutes per week of moderate intensity physical activity), or high (> 3000 MET x min/week or > 750 minutes per week of moderate intensity physical activity) [70, 71].

Sleep quality will be evaluated using the question of sleep quality assessment of the Pittsburgh Sleep Quality Index (PSQI) [72]. Each participant will answer, “During the past week, how would you rate your sleep quality overall?” and rate their self-perception of sleep quality as very good, fairly good, fairly bad, or very bad. In addition, the participant will answer two questions about how pain has interfered with sleep, classifying it in a dichotomous scale (yes or no) if "Are you awake in the middle of the night or early in the morning because of your pain?" and "Have you had trouble falling asleep because of your pain?”.

Data collection will be performed by using a standard questionnaire. The completion of all questionnaires will be supervised by an examiner for clarification in case of uncertainties and will last approximately 30 minutes per participant. The schedule will be performed as presented in Fig 1.

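### The mediation analysis takes mediators measured before randomisation, so the true indirect effect is zero by design; the error is confined to a tertiary analysis

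*Protocol article*

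**What the plan says.** The Tertiary analysis section of the protocol article gives the aim as a "mediation analysis to understand whether sociodemographic factor, pain characteristics, and psychosocial factors affect the primary outcomes". It then sets out the model:

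- **X:** "considering the treatment group as independent variable (X").
- **Y:** pain intensity and functional limitation, in separate models.
- **M:** "sociodemographic factor, pain characteristics, and psychosocial factors as mediators (M").
- **Form and timing:** simple mediation, "considering one variable per model, and we will use data collected at baseline".

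Two other sections fix when baseline is. Under Data collection and management, "characteristics at baseline assessment will be collected immediately before randomisation". Under Randomisation, allocation, and blinding procedures, "After the initial assessment, participants will be randomised to one of two groups". The Baseline assessment section lists the sociodemographic candidates: "demographic (age, sex, weight, height, house income, marital state, profession, and education level").

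Psychosocial factors are also followed after randomisation. The Secondary analysis section models change in "psychosocial factors from baseline to each 5, 10- and 26-weeks after randomisation". The Subgroup analyses section plans none.

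**The concern.** A mediator lies on the causal path from treatment to outcome, so treatment must be able to change it. A value recorded before allocation cannot be changed by allocation. Age, sex, height and education could not be changed by treatment at any visit.

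Followed as written, the analysis can give only two kinds of result: a null that says nothing about mechanism, or a positive that reflects chance imbalance between the arms. Neither answers a mediation question, at any sample size.

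The stated aim does not fit the model either. Whether baseline factors affect the outcomes is a question of prognosis or, if moderation was meant, of effect modification. A mediation model with treatment as X targets neither.

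**Working it through.** **Inputs.** From the protocol: X is randomised 1:1; M is measured before randomisation; 210 participants, with 15% allowed for post-randomisation exclusion. The plan states no figure for the mediation analysis, so there is none to reproduce. Two sample sizes were used: 210, and 210 × 0.85 = 178.5, taken as 178. Assumed: the M–Y correlation within arm (b, with M and Y standardised) and the number of candidates k.

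**Step 1: the target quantity.** In simple mediation, M = i₁ + aX + e₁ and Y = i₂ + c′X + bM + e₂, and the indirect effect is a × b. M precedes a random X, so a = 0 and a × b = 0 × b = 0 for every b.

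**Step 2: what the estimate does.** With equal arms, the standard error of the estimate of a is about 2/√n: 2/√178 = 0.150 and 2/√210 = 0.138. The estimated indirect effect should therefore scatter around zero with SD of about b × 2/√n. At n = 178 that is 0.3 × 0.150 = 0.045 and 0.5 × 0.150 = 0.075. Simulation agrees (10,000 trials per setting, true treatment effect of 0.4 SD, 5% level):

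| n | b | Mean indirect effect | SD | X-to-M path significant | Both paths significant | Sobel test significant |
|---|---|---|---|---|---|---|
| 178 | 0 | −0.0001 | 0.012 | 4.9% | 0.28% | 0.01% |
| 178 | 0.3 | −0.0003 | 0.046 | 4.9% | 4.8% | 2.3% |
| 178 | 0.5 | 0.0010 | 0.075 | 4.7% | 4.7% | 3.9% |
| 210 | 0 | 0.0000 | 0.010 | 5.2% | 0.23% | 0.01% |
| 210 | 0.3 | −0.0001 | 0.042 | 4.8% | 4.7% | 2.7% |
| 210 | 0.5 | 0.0001 | 0.070 | 4.9% | 4.9% | 4.3% |

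When M is prognostic, the rate of false mediation under the joint test is essentially the rate at which baseline M differs between arms by chance.

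**Step 3: several candidates.** For k independent, strongly prognostic candidates, the chance of at least one false mediator is at most 1 − 0.95^k:

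- k = 5: 1 − 0.95^5 = 23%
- k = 10: 1 − 0.95^10 = 40%
- k = 20: 1 − 0.95^20 = 64%

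The second outcome does not raise these ceilings. The X-to-M test for a given M is the same in the pain model and the function model, and a joint-test false positive in either model requires that shared test to be significant.

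**Step 4: how attainable the ceilings are.** Independent variables each correlated r with Y explain k × r² of its variance, which cannot exceed 1.

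- At r = 0.4, at most six fit (6 × 0.16 = 0.96), giving 1 − 0.95^6 = 26%.
- At r = 0.3, at most eleven fit (11 × 0.09 = 0.99), giving 1 − 0.95^11 = 43%.
- Twenty fit at r = 0.2 (20 × 0.04 = 0.80). There the joint-test rate in a separate run of 4,000 simulated trials was 3.8% per model, giving 1 − 0.962^20 = 54% for one outcome.

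The 64% figure is therefore an upper bound, not an expectation.

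**The case against.** **A softer reading of the timing.** In a condensed article, the reference to baseline data might cover only the fixed factors. This is weak. The phrase belongs to the description of the mediator analysis as a whole, and the section names no follow-up value of M. Even on that reading, sociodemographic variables remain listed as mediators. Nor is this a detail left to an analysis plan: the article itself fixes X, Y, M, the model form and the data timing.

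**Size.** A reader might assume 20 baseline variables and two outcomes, count 40 independent models, and conclude that two false mediators are expected (40 × 0.05) with an 87% chance of at least one (1 − 0.95^40). The documents do not support this. They give no number of candidates, the two outcomes share one X-to-M test per candidate, and 20 independent variables cannot all be strongly prognostic. Two is a ceiling on the count of false-positive models, which would tend to come in pairs, and some listed variables may hardly be prognostic at all.

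**Importance.** The objection that this is a tertiary analysis stands in full. The primary and secondary comparisons, the sample size and the safety reporting do not depend on it.

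**Harm.** A reader might also infer that false mediators will be published as the mechanism of neural management. The protocol makes no such claim; its stated aim concerns factors that affect the outcomes. To that extent the defect is partly a wrong method attached to a prognostic question. That does not rescue the method.

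**Conclusion.** The point holds. As specified, the mediation analysis estimates a quantity known in advance to be zero, because every mediator is measured before randomisation. This follows from the protocol's own timing and needs no numerical assumption.

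The false-positive rate is at most about 5% per candidate when M predicts the outcome, and about 0.2–0.3% when it does not. The figures for several candidates are ceilings that rest on an assumed k, on independence and on strong prognostic value. The consequence is limited to this tertiary analysis; nothing here weakens the primary comparison at 10 weeks. It should be corrected before the data are analysed.

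**What to change.** Rewrite the mediation paragraph of the Tertiary analysis section:

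1. **Keep as mediators only listed factors that treatment can change:** psychosocial factors, and any pain characteristics re-measured at follow-up that are not themselves the outcome of the model. Use the 5-week value as M and the 10-week pain or PSFS score as Y, adjusting for baseline M and baseline Y. M is not randomised, so label the results exploratory.
2. **Remove sociodemographic variables and other baseline-only factors from the mediator list.** If their role is of interest, analyse them as prognostic factors for the outcome, which matches the stated aim.
3. **If effect modification is what is meant,** call it an exploratory treatment-by-baseline interaction and bring the Subgroup analyses section into line.

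Adding mediators that the section does not list, such as conditioned pain modulation or sciatic neurodynamic measures, is optional and not needed to repair the error.

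The cost is wording only. The Outcomes measures and Secondary analysis sections already schedule psychosocial factors at 5 and 10 weeks, so no new visit or measurement is required for them.

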#### Subgroup analyses

No subgroup analysis is planned for this study.

#### Sensitivity analysis

A sensitivity analysis will be performed, including different imputation techniques for missing data to assess the robustness of the primary analysis and results for a per-protocol analysis to assess the efficacy of the protocol.

### Plans for communicating important protocol amendments to relevant parties

Important protocol modifications such as changes to eligibility criteria, outcomes, or analyses will be notified to relevant parties (e.g., Research Ethics Committee, researchers, participants, and journal of publication). Also, participants will be asked to give feedback on any change in protocol. Participants’ feedback regarding the study participation satisfaction will be collected by MedRisk questionnaire at study closure.
